### Statistical methods

#### Statistical power and sample size calculation

Primary analyses are limited to children with anemia at enrollment. At the end of 6 months, a difference of at least 12 % in the cure rate of anemic children is required if the intervention is considered to have sufficient public health utility to warrant its cost and effort [47–49]. We estimate that the 12 % reduction in proportion of anemic children at 6 months would occur due to a cure rate of 30 % in the control group (IFA alone) and 42 % in the experimental arm where children receive IFA plus the community-based parental intervention. To detect a 12 % difference in 6-month anemia cure rates at an alpha level of 0.05 for a two-tailed test, with 80 % power, a total unadjusted sample size of 500 children with anemia is required, which after adjustment for clustering (design effect = 2.2) results in a sample size of 1,100 children with anemia. The design effect assumes an intracluster correlation coefficient (ICC) of 0.05 and 25 participating children with anemia per village. The anticipated degree of intracluster correlation was selected based on results from several recent trials of interventions on anemia [47–49]. We further allow for a 10 % loss to follow-up of children identified with anemia at baseline, yielding a final sample size of 610 children with anemia per arm (1,220 in all). We will recruit 30 clusters per trial arm to accommodate potential losses of clusters if LHWs should stop working, resulting in loss of an entire cluster. Thus, power will be greater than 80 %. Analyses will also consider prevalence of anemia at 6 months among all participating children regardless of their baseline anemia status. Based on an estimated prevalence of 50 % anemia at baseline in each village, the number of children required will be 1,220 in each trial arm.

#### Statistical analysis

The primary analysis will follow the intention-to-treat principle, whereby all children regardless of whether they received the full intervention or not will be included in the analysis of the group to which they were randomized. Data will be analyzed at the individual level adjusting for clustering using generalized estimating equation (GEE) extensions of logistic regression for presence or absence of anemia while similar extensions of linear regression will be used to model individual hemoglobin levels [50]. All models will adjust for the stratification factor (the number of children per village). The effects of explanatory variables such as age, sex, socioeconomic status, literacy, nutritional parameters, and maternal anemia status will also be explored. Secondary analyses will consider the effect of adjustment for these potential explanatory variables on the estimated intervention effect using multivariable regression models. All tests will be declared statistically significant at the 0.05 level (two-tailed).

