### Protocol of recruitment

From the list of all children < 6 years registered in each village by the LHW in charge of the ADC, the research team will generate an eligible 12–59 month child list. Using this list, the LHW will mobilize participants and their mothers to the village ADC for study enrollment. Recruitment will occur at the village ADC and last for approximately 2 days. Additional house visits will be made on recruitment days to identify reasons for non-attendance of participants on the list (for example, those who are too sick, traveling, or migrating] and to help mobilize those who forgot to visit the ADC. Mothers/caregivers of all eligible children, who after being provided information about the trial indicate willingness to participate and an intention to live in the village for at least 6 months after enrollment, and those in the intervention arm indicating a willingness to receive LHW-led counseling will be enrolled after providing written informed consent (Fig. 1). Where recruitment is <80 % of the eligible list, an additional recruitment day will be allocated. Children who do not fulfill the inclusion criteria during recruitment sessions are not eligible for future recruitment.

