### Protocol of data collection

At study entry, a baseline questionnaire will record participant information. An additional file shows this in more detail [see Additional file 1]. Participants will also have a baseline sample of anticoagulated venous blood obtained to detect anemia and measure serum ferritin. All recruited participants will have a hemoglobin value estimated using an automated cell counter (Sysmex 405, Transasia laboratory systems, Japan). Within a few days the research team will provide mothers/caregivers with results of the hemoglobin values and anthropometry, and cluster LHWs with a list of anemic and non-anemic children. The list will permit LHWs in each cluster to organize the delivery of dose appropriate IFA to anemic and non-anemic children and to identify mothers of anemic children for delivery of monthly education and counseling.

The date of delivery of the first month’s supply of IFA to the mothers of children in a cluster will herald the start of the intervention in that cluster. LHWs will deliver IFA to mothers of non-anemic children at the ADC during routine monthly visits. LHWs will typically deliver IFA together with education and counseling to mothers of anemic children at their homes. From the second visit onward, adherence data will be collected by the LHW, and the remaining IFA pills/empty strip will be obtained from the mother. In the control arm, LHWs will deliver IFA as usual in the setting of the ADC and will not deliver education and counseling to mothers of anemic children or collect monthly IFA adherence data. Approximately 6 months from the day of delivery of the first IFA supplement, the research team will perform a follow-up visit to collect 24-hour dietary recall data, anthropometry, and information on adherence to IFA in the previous month from all enrolled participants. During this time, a repeat phlebotomy to estimate hemoglobin is performed for all participants in the cluster, and the trial is completed.

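### The primary cure-rate model omits each child's baseline hemoglobin: valid as planned, but it gives up some precision and some protection against imbalance in severity

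*Protocol article*

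**What the plan says.** The sample size section sets the population: "Primary analyses are limited to children with anemia at enrollment". The section on intervention components defines anemia as hemoglobin from 8 to 11 g/dL. The Outcomes section makes the difference in cure rates at 6 months the primary outcome.

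The Statistical analysis section gives the model as "generalized estimating equation (GEE) extensions of logistic regression for presence or absence of anemia" and states one covariate rule: "All models will adjust for the stratification factor (the number of children per village". It then lists further variables: "The effects of explanatory variables such as age, sex, socioeconomic status, literacy, nutritional parameters, and maternal anemia status will also be explored". Their place is defined next: "Secondary analyses will consider the effect of adjustment for these potential explanatory variables on the estimated intervention effect using multivariable regression models".

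The child's baseline hemoglobin appears neither in the rule for all models nor among the named explanatory variables. It is available for everyone, because under Protocol of data collection "All recruited participants will have a hemoglobin value estimated using an automated cell counter".

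**The concern.** Every child in the primary analysis starts inside a band 3 g/dL wide, and cure, read here as no longer being anemic, means leaving that band at the top. A child who starts just under the upper limit would be expected to cross it more readily than one who starts near 8 g/dL. Adjusting for anemia yes or no cannot capture this, since all these children are anemic at baseline. Only the continuous value can.

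Two things are at stake. Leaving out a prognostic baseline value gives up precision. It also leaves the estimated cure-rate difference exposed to any difference in starting severity between the arms. Stratification by village size does not balance severity.

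**Working it through.** **1. The plan's own figure.** Inputs from the sample size section: cure 30% vs 42%, "at an alpha level of 0.05 for a two-tailed test", 80% power, ICC 0.05, 25 anemic children per village, 10% loss.
- Per arm, pooled variance: [1.96·√(2·0.36·0.64) + 0.842·√(0.30·0.70 + 0.42·0.58)]² / 0.12² = (1.330 + 0.567)² / 0.0144 ≈ 250, so 500 in total, as stated.
- Design effect: 1 + 24·0.05 = 2.2, and 500·2.2 = 1,100, as stated.
- Loss: 1,100/0.9 = 1,223 after rounding up, against 1,220 stated.
- With all 60 villages and 10% loss: 60·25·0.9 = 1,350 children, 22.5 per village, design effect 2.075, power 89%.

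None of these figures relies on covariate adjustment.

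**2. How large a chance imbalance is.** Assumptions: population hemoglobin mean 11 and SD 1.2 g/dL (which gives the plan's 50% anemia), cut to 8–11, so SD about 0.67 among the anemic. Take 18 evaluable children per village (1,220/60·0.9 ≈ 18), or 540 per arm. The standard error (SE) of the between-arm difference in mean baseline hemoglobin is:
- with no village correlation: 0.67·√(2/540) = 0.041 g/dL;
- with baseline ICC 0.05: 0.041·√(1 + 17·0.05) = 0.056 g/dL.

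A 0.1 g/dL difference is therefore 1.8 to 2.4 SE. A 0.2 g/dL difference is 3.6 to 4.9 SE, with a two-sided probability of about 0.0003 or less.

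**3. What an imbalance does to the result.** The documents do not give the link between baseline hemoglobin and cure, so it is an assumed range.
- *Simulation A* (30 villages × 18 children per arm, 1,500 trials per setting, correlation of baseline with 6-month hemoglobin 0.3, 0.5, 0.7). The risk difference without hemoglobin in the model moves by 0.096, 0.161, 0.247 per g/dL, which is about 1.0, 1.6, 2.5 points per 0.1 g/dL. A one-SE chance imbalance moves it from 0.096·0.041 = 0.4 points to 0.247·0.056 = 1.4 points.
- *Simulation B* (60 villages × 22 children, 400 runs per setting, log-odds of cure 0.3, 0.6, 1.0 per SD of baseline hemoglobin, SD 0.65 g/dL). The shift is 8.6, 14.3, 18.8 points per SD. Multiplied by 0.1/0.65, that is 1.3, 2.2, 2.9 points per 0.1 g/dL, in broad agreement with A.

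**4. What adjustment gains.** Variance of the risk difference, adjusted over unadjusted:
- A: SD 0.0356 vs 0.0353, 0.0350 vs 0.0343, 0.0345 vs 0.0328. The variance factors are 1.01, 1.04, 1.11, a reduction of about 1% to 10%.
- B: ratios 0.97, 0.93, 0.82, a reduction of about 3% to 18%. With no prognostic link the ratio is 1.00.

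**5. A limit on the simulations.** With 540 per arm and a cure ICC of 0.05, SE = √[(0.21 + 0.2436)/540 · 1.85] = 0.039 and power is about 86%. Simulation A's SDs imply a smaller cure ICC: 0.0345²/0.00084 = 1.42, and 0.42/17 ≈ 0.025; likewise 0.0356 gives about 0.030. Its simulated powers of 91% to 95% are therefore too high and are not used here. With more unexplained variation between villages, the share of variance removed may be somewhat smaller than in step 4.

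**The case against.** The strongest reply is that nothing is broken. Under randomization a chance difference in baseline hemoglobin is already in the standard error and biases neither the estimate nor the test. A one-SE imbalance moves the result by 0.4 to 1.4 points, which is small beside a standard error of 3.5 to 3.9 points. This stands. A reader might infer that the omission biases the primary result or leaves the trial short of power; the documents support neither.

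A reader might also infer a systematic imbalance from the enrollment conditions, which differ by arm: "those in the intervention arm indicating a willingness to receive LHW-led counseling will be enrolled after providing written informed consent". A standard error would not cover that. But the protocol gives no evidence that severity differs between enrolled groups. Hemoglobin results follow enrollment, and adjusting for hemoglobin would not remove selection on willingness or motivation. Differential enrollment is a reason to want the adjustment, not proof of bias.

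It can be said that the covariate list is open-ended and that a condensed article leaves detail to an analysis plan. That carries less weight, because the article does state the covariate rule for all models and assigns other adjustment to secondary analyses. An open secondary list does not put hemoglobin into the primary model.

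Finally, a prognostic covariate in a logistic GEE turns the odds ratio into a conditional one, while the primary outcome is a difference in cure rates. This is correct and shapes the fix.

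**Conclusion.** The point holds as a recommendation to improve the primary model, not as the correction of an error. The stated model leaves out the most direct baseline predictor, and that predictor is already collected. The cost is a variance roughly 1% to 18% larger than it could be, and an estimate that shifts by about 1 to 2.5 points per 0.1 g/dL of imbalance, where typical chance imbalance is 0.04 to 0.06 g/dL. These sizes rest on an assumed hemoglobin distribution and an assumed strength of association. If baseline hemoglobin were not prognostic, nothing would be gained. Shifts of 2 to 5 points would need a 0.2 g/dL imbalance, which chance alone would hardly ever produce under these assumptions. The stated sample size and power stand.

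**What to change.** In the Statistical analysis section, specify the primary GEE logistic model as cure at 6 months on arm, village-size stratum and continuous baseline hemoglobin, with age optional. From that model, report the standardized (marginal) difference in cure rates with a cluster-robust confidence interval as the primary estimate, so that it is on the scale of the 12-point target. Keep the stratum-only model as a sensitivity analysis.

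This should be fixed before outcomes are examined by arm, including at the planned interim analysis. Adding hemoglobin after an imbalance has been seen would look data-driven. No new data are needed. The cost is a few lines of wording, one standardization step, and an odds ratio that must be labeled as conditional.

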### Ethical issues

#### Ethical approval

The study was approved by the St. Johns National Academy of Health Sciences Institutional Ethical Committee (IEC 115/2012).

#### Information and informed consent

Information about the trial is provided to community leaders and mothers through the LHW. Written and verbal information about the trial is provided in English and Kannada (the local language). Documents translated into Kannada are validated through back translation. All participant mothers/care providers are provided with study information prior to enrollment for review. Individual informed consent is obtained from mothers/care providers of selected children, and is recorded by signature or thumbprint. Mothers/care givers will also be informed that participation of their child in the study is completely voluntary and that they may withdraw from the study at any time.

#### Monitoring of side effects and trial supervision

Details regarding side effects to IFA supplements will be collected by the LHW and notified to the research team. In the event of side effects that are deemed related to IFA (either by the LHW or the research team), participants are advised by the LHW to discontinue IFA and report to the primary health center for evaluation. Since the intervention under comparison is non-invasive, the IFA supplements in the protocol follow national recommendations, and the setting is not a malaria endemic region, the occurrence of serious adverse events (SAEs) is unlikely. An interim analysis of the trial will take place when all subjects have been recruited and all 30 clusters have completed 3 months of delivery of the intervention. This analysis will be conducted in a blinded manner by an independent data safety and monitoring board (DSMB) consisting of experts in clinical medicine, epidemiology, and statistics. The primary aim of the interim analysis is to assess if the intervention arm shows a clearly better, or worse, outcome than the control arm as well as to evaluate SAEs.

## Discussion

This is the first cluster randomized control trial (CRCT) designed to evaluate an intervention that includes both lay health workers and parents to complement India’s existing national health policy for combating anemia in children, one of the most pernicious and common nutritional health burdens among individuals in resource-limited settings [3, 6, 10, 51]. The present evaluation adopts a theory-based approach to investigate the causal chain through which the proposed intervention is expected to have its impact (Fig. 2). We employ qualitative methods to understand the perceptions and experiences of LHWs actually delivering the intervention and the context and process of the interventions delivery [52]. Results from this contextually relevant intervention will be used to establish whether it is possible to improve anemia cure rates in anemic children in India with relatively limited efforts targeted to the mothers of such children.

The CRCT design, whereby groups of individuals are randomly allocated to different interventions, has the potential to provide unbiased estimates of the impact of interventions delivered at the community level (in this case children in a village eligible to attend the village day care). A major strength of this trial is that it attempts to maximize participation at both the cluster and individual levels. For instance, LHWs in both arms of the study will be provided with training, support, and resources to achieve intervention goals, and will encourage cluster-level participation to minimize drop-out rates. Furthermore, randomization will be an inclusive process with active involvement and participation of the LHWs. During recruitment, the research team will actively support LHWs during periods of stress (wage-related agitations, unscheduled ADC closures for local holidays, and breaks during which LHWs perform other tasks such as immunization). The research team will perform door-to-door visits for eligible children who failed to attend the ADC after mobilization by the LHW to identify reasons for the mothers’ lack of attendance. Analysis of all this data will provide clarity regarding participation in this trial and could address concerns related to selection bias.

Anemia has been a public health problem for several decades [3, 6] and is in great need of effective control programs. India bears a large portion of the burden of anemia in Asia, with close to 100 million anemic children [2, 6]. The need for effective intervention studies addressing anemia is particularly relevant to rural Indian communities, where the prevalence of anemia is highest. However, there is an increasing appreciation that such studies should not only evaluate if interventions work, but also how they work, thereby enhancing the policy implications of such evaluations [52, 53]. In order to maximize policy relevance, it is essential to understand the context of the research, the related policymaking processes and to engage key stakeholders. To achieve this, we intend to continuously engage with the health authorities at state, provincial, and district levels. Inadequate IFA supplies have been previously noted to be a major limitation to the success of anemia control in low-middle income settings [28]. Thus, instead of procuring IFA commercially, the Karnataka state health officials will be involved and the state infra-structure will be utilized to ensure that IFA is made available for the trial. These efforts could eventually lead to greater sensitization of the health department regarding IFA availability and recognition of the need for enhanced LHW capacity to screen and manage anemia in Karnataka. Conducting research in rural communities, especially in an Indian context, raises a number of practical and logistic issues. The research team has partnered with an experienced field research agency that has an established track record of development research in the Chamarajnagar district. This team will work collaboratively, coordinate with the government, involve community leaders from villages in the study area, and make participants stakeholders in their healthcare, all of which will contribute to the successful conduct of the trial.

Indeed, the novelty of this cluster RCT consists of its real-life setting evaluation of education and counseling combined with monitoring of parental compliance in connection with the delivery of IFA supplements to attenuate the public health problem of childhood anemia. All intervention components will be delivered by a community LHW, therefore relying on local human resources. Furthermore, the intervention will use healthy local dietary practices to positively influence the nutritional behaviors of children and parents. If successful, such an approach could profoundly shift the attention of anemia control policy towards a diet-focused rather than a supplementation-focused approach. Once effectiveness in real-life conditions is ascertained, all the above features of the intervention will collectively ensure high potential for sustainability and scaling-up of the intervention. The intervention may lead to improved hemoglobin values and reduced anemia prevalence among 12–59-month children in the short term [18, 26] and could result in better cognitive outcomes in these children over the long term [18, 54–56]. If effective, the intervention could be implemented on a larger scale to determine if such local effects may have a wider positive health effect nationally. Final results from this intervention trial are expected in mid-2016.

## Trial status

The trial commenced recruitment in November 2014 and intends to complete recruitment in July 2015.

## Abbreviations

ADC: Anganwadi day care center
CHW: community health worker
Hb: hemoglobin
IDA: iron deficiency anemia
IFA: iron and folic acid
Iron + Initiative: National Iron plus initiative
LHW: lay health worker
NNACP: National Nutritional Anemia Control Programme
